### Secondary objectives and secondary endpoints

The secondary objectives are as follows:
To evaluate the OS at the 5-year follow-upTo assess different strategies of RT in terms of fertility and obstetric outcomesTo compare the incidence of perioperative complications of different surgical approachesTo compare major perioperative complications within 28 days after surgery and major postoperative complicationsTo determine the general and specific QoL

Secondary endpoints will therefore be the following:
All-cause mortalityFertility outcomes consisting of cervical incompetence, natural pregnancy, and infertility treatment such as intrauterine insemination or IVF-ET; obstetric outcomes consisting of the time interval between the RT surgery and pregnancy; the overall mean length of time during which conception was attempted; the number of pregnancies; the mode of delivery; and the outcome of each pregnancy, such as spontaneous abortion, induced abortion, drug abortion, preterm birth, premature rupture of membranes, fetal growth restriction, and full-term birthPerioperative complications consisting of injury of the ureter, bladder, bowel, blood vessels, or nerves, and vaginal bleeding, and postoperative complications consisting of postoperative pelvic infection, pelvic lymphocele, intrauterine infection, Asherman syndrome, abnormal menstruation, urinary tract infection, hydronephrosis, intestinal obstruction, chronic pain, varices at the site of uterovaginal anastomosis, and fistula formationMajor perioperative and postoperative complications consisting of early postoperative complications (cerebrovascular, pulmonary, and renal diseases; ileus; abdominal wound complications; septicemia; thromboembolism; and lymphocele formation and secondary infection) and delayed postoperative complications (lymphedema, vaginal evisceration)QoL assessment comprising the authorized Chinese edition of EORTC QLQ-C30 [13] and its CC module QLQ-CX24 [14], the 19-item Female Sexual Function Index (FSFI) [15], and the PFIQ-7 questionnaire [16].

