### Safety and adverse events

The adverse events and their severity will be judged by the criteria of the Common Terminology Criteria for Adverse Events [18]. This trial will be conducted in compliance with this study protocol.

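### The major complications endpoint is a closed list of event types with no severity threshold, and it leaves out organ and vessel injury and fistula

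*Protocol article*

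**What the plan says.** All the definitions stand in the Protocol article, *Secondary objectives and secondary endpoints*.

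- **Objective.** Beside a general comparison of perioperative complications, there is a separate objective to "compare major perioperative complications within 28 days after surgery and major postoperative" complications.
- **Ordinary complications endpoint.** Its perioperative part covers "injury of the ureter, bladder, bowel, blood vessels, or nerves, and vaginal bleeding". Its postoperative part begins with "postoperative pelvic infection, pelvic lymphocele, intrauterine infection" and ends with fistula.
- **Major complications endpoint.** This is given as major "perioperative and postoperative complications consisting of early postoperative complications (cerebrovascular, pulmonary, and renal diseases; ileus", then wound complications, septicemia, thromboembolism and "lymphocele formation and secondary infection". A second group follows: "delayed postoperative complications (lymphedema, vaginal evisceration").

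Severity appears elsewhere, under *Safety and adverse events*: "The adverse events and their severity will be judged by the criteria of the Common Terminology Criteria for Adverse Events". No section links a CTCAE grade to the word major.

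**The concern.** A label such as major tells a reader that the events counted are the serious ones. Here the label is assigned by type of event, and the types chosen do not match that meaning. Several entries can be mild (wound complications, ileus, lymphedema), while injuries and fistulas that can be severe are outside the list altogether.

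The safety comparison carries weight in this trial. *Background* and *Discussion* present the minimally invasive route partly through lower morbidity and faster recovery, so complications are a main counterweight to the oncologic result. If the abdominal arm had more low-grade wound problems, its major rate would rise without any excess of serious harm. If either arm had more visceral or vascular injury, the major rate would not show it. Both statements are conditional: the documents give no complication rates by route.

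**Working it through.** No arithmetic on rates applies. The check is an item-by-item comparison of the two lists, followed by a search for a severity rule elsewhere in the article.

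**Step 1: compare the lists.**

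| Event type | Ordinary list | Major list | Severity stated |
|---|---|---|---|
| Ureter, bladder, bowel, vessel or nerve injury | yes | no | no |
| Vaginal bleeding | yes | no | no |
| Fistula | yes | no | no |
| Lymphocele | yes | yes (see step 4) | no |
| Intestinal obstruction / ileus | as obstruction | as ileus | no |
| Abdominal wound complications | no | yes | no |
| Lymphedema | no | yes | no |
| Vaginal evisceration | no | yes | no |
| Septicemia, thromboembolism | no | yes | no |
| Cerebrovascular, pulmonary, renal disease | no | yes | no |

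The major list has six early entries separated by semicolons and two delayed entries, so 6 + 2 = 8. None of the eight carries a grade, symptom or reintervention criterion. Some, such as septicemia, are serious by nature. Others, such as lymphedema and wound complications, span mild to severe.

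**Step 2: compare the endpoint with its objective.** The objective concerns major perioperative complications. The ordinary list names six types as perioperative: five sites of injury plus vaginal bleeding, 5 + 1 = 6. None of the six is in the major list. That list is titled perioperative and postoperative, but its two groups are early postoperative and delayed postoperative. No intraoperative event appears in it.

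**Step 3: ask whether the list is closed.** It is introduced as what the endpoint consists of. Where the same section means examples, as for infertility treatment or pregnancy outcomes, it says so with different wording. The natural reading is that the list is complete.

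**Step 4: read the lymphocele entry.** The words "lymphocele formation and secondary infection" form one entry. They can mean lymphocele of any kind plus secondary infection, or lymphocele that has become infected. The text does not settle which.

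**Step 5: look for a rule elsewhere.**
- *Safety and adverse events* names CTCAE for severity but does not define major.
- *Description of the parameters for assessing efficacy endpoints* says that surgeons or a consulted specialist assess complications, without a rule for calling one major.
- Table 1 schedules perioperative complications at 10 to 14 days and postoperative complications at four weeks, with no grade shown.
- *Statistics* does not mention the term.

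**Result.** Followed literally, a bowel injury needing major repair is an ordinary complication, and a mild lymphedema is a major one.

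**The case against.** The other side has several fair points.

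- **Lymphocele.** A reader might infer that any lymphocele, even a silent one, counts as major. The text does not establish this. If the entry means infected lymphocele, the two lists fit together on this item: plain lymphocele is ordinary and infected lymphocele is major. Table 1 also lists no imaging at the early complication visits. This stands, so the point should not rest on lymphocele. Organ injury, fistula, wound complications and lymphedema carry it without that item.
- **Counting in two endpoints.** A reader might infer that an event appearing in both endpoints is an error. It is not: a major event may properly count in an overall endpoint as well. Treating ileus and intestinal obstruction as the same event is also an inference.
- **Loss of power.** One could assume rates of serious and low-grade events and compute a dilution. The documents give no complication rates and power no complication endpoint. Such a calculation would also have to model the omitted injuries. No figure is supportable.
- **Information is not lost.** Organ injury and fistula remain named secondary outcomes, and CTCAE severity is planned, so a graded safety table may well be produced. Serious consequences of an injury could also enter the major list by another entry, such as septicemia. This limits the harm, but it does not make the major rate mean what its name says.
- **Detail left to a fuller document.** How grades enter tables is often settled in the analysis plan. Here, however, the article states both lists in full. A later plan that used a grade threshold would depart from the stated definition instead of completing it.

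**Conclusion.** The point holds as a misclassification written into one secondary endpoint. The definition goes by event type alone, omits visceral and vascular injury and fistula, contains no intraoperative event although its objective concerns perioperative complications, and admits events that may be low grade. The resulting major complication rate could mislead in either direction.

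This rests on two readings: that the list is complete, and that no grade is implied by the word major. Both follow from the text as printed. The size of any distortion in the comparison between arms is unknown.

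The change is worth making before complications are compared by arm, but it is a matter of one unpowered secondary endpoint. The primary DFS analysis and the sample size are untouched.

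**What to change.** Define a major complication as any listed event at or above a prespecified CTCAE grade, for example grade 3 or higher. Apply the grade to all intraoperative and postoperative event types in both current lists, with organ and vessel injury and fistula included. Report events within 28 days separately from later ones, which matches the objective and the four-week visit in Table 1. Keep the type lists as descriptive categories, and state that a major event also counts in the overall complications endpoint. Clarify whether the lymphocele entry means infected lymphocele only.

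The cost is a wording change to one endpoint and a grade field for each complication on the case report form. The article plans severity grading but does not show that the form captures it. Fewer events will be labelled major. Grading would still be done by unblinded surgeons or consulted specialists, so the change corrects the definition and does not remove assessor bias. Treatment, visits and sample size need no change.

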### Description of the parameters for assessing efficacy endpoints

The primary endpoint is a composite endpoint, which will be collected at each visit. Surgical complications will be assessed by surgeons and/or a specialist if he or she has been consulted for a complication. Obviously, a double-blinded trial was not feasible, i.e., the surgeons and clinicians managing the patients have to explain the operation method and risks to the patients, and in turn, the patients must sign their informed consent. However, the information of patients and surgeons are blinded to performers dealing with data analysis.

### Learning curve

In this study, all surgeons have been qualified by the existing continuous clinical data and survival outcomes of at least 10 patients with early-stage CC who have undergone RT, including at least 5 cases of MIRT. Meanwhile, the surgeons should provide all surgical reports and at least two integrated copies of surgical videos as the competence of these surgeries. These data and videos will be presented as supplementary material for the final report. The survival outcomes are used to assess the learning curves of participating surgeons, and the videos are used to assess the surgical skills.

### Surgical treatment

Patients with early-stage CC who are eligible for enrollment will be randomly assigned to the MIRT group or ART group. Evaluation of the pelvic nodes in patients with early-stage CC will be performed. The pelvic lymph nodes may be assessed with a complete lymphadenectomy or via sentinel lymph node mapping. Surgical details, including uterine artery preservation, the cerclage material and position of knot placement, and the method to prevent cervical stenosis, will be recorded in the surgical records.

### ART

Entry into the abdomen may be accomplished via a midline vertical incision to gain adequate access to the pelvis. After excising the pelvic lymph nodes, the paravesical and pararectal spaces are developed. The round ligaments are grasped with Kelly clamps for uterine manipulation, and the vesicocervical space is developed to dissect the bladder off the cervix. Care is taken to preserve the ovary pelvic funnel ligaments and utero-ovarian vessels, as these are the main blood supply to the remaining uterus. The uterine vessels are preserved, while their descending branches are resected at the level of the isthmus. Once complete ureterolysis is performed to the tunnel of Wertheim, the uterine vessels are divided at their origin from the hypogastric vessels. The parametria and paracolpos are mobilized with the trachelectomy specimen. The posterior cul-de-sac is incised, and the uterosacral ligaments are divided at their origin. The vagina is then incised to perform an anterior colpotomy 1–2 cm distal to the external cervical os. This incision is then carried circumferentially until the specimen is completely separated from the vagina. The lower uterine segment is estimated, and clamps are placed at the level of the internal os. The cervix is then incised with a knife approximately 5 mm below the internal os. Patency of the remaining cervical canal may be achieved with the use of a Foley or Malecot catheter followed by the placement of an endocervical cerclage. The lower uterine segment is then sutured to the vaginal mucosa via interrupted or continuous sutures [17].

### MIRT

The procedure with either a laparoscopic or robotic approach is the same with regard to the abdominal approach. A uterine manipulator must be avoided. A vaginal excision must be made under vaginal exposure rather than under peritoneal exposure.

### Safety and adverse events

The adverse events and their severity will be judged by the criteria of the Common Terminology Criteria for Adverse Events [18]. This trial will be conducted in compliance with this study protocol.

### Data management

All medical information required according to the protocol will be collected via the case report forms based on the website, facilitating the real-time, central assessment of the data completeness and patient follow-up. This information will include demographic data, the surgical approach, the skin-to-skin operative time, EBL, and the surgical energy devices. The pathogenic material will also be collected, including the results regarding the tumor histology subtype, FIGO stage, grade (well, moderately or poorly differentiated), tumor size, depth of stromal invasion, LVSI, lymph node status, and surgical margin status. After RT, data on surgical complications, bladder/intestinal function recovery, QoL, fertility and obstetrics outcomes, and disease recurrence and survival information will also be followed.

The questionnaires will be completed, the ovarian reserve function will be evaluated, and a urodynamic study (UDS) and anorectal manometry will be assessed within 4 weeks before surgery, at 4 months postoperatively, at 12 months postoperatively, and then once a year thereafter. After the RT (Table 1), the patients will be required to attend the customed follow-up regularly, at 3- to 6-month intervals in the first 2 years after completing the treatment, 6- to 12-month intervals from the third to the fifth year after treatment, and then at 1-year intervals thereafter. The effects of the follow-up scheme (pelvic examination, the ThinPrep cytological test and/or human papillomavirus testing, transvaginal ultrasonography, an abdominal ultrasound scan, chest radiography, and serum tumor marker, i.e., squamous cell carcinoma and Ca125) will be evaluated at each visit.

**Table 1 Tab1:** Lists of clinical assessments at different time points

Check-up time	Inspection items	Documentors	Directors
Within 4 weeks before RT	Urodynamic assessment	CRF	Research centers
	Anorectal manometry	CRF	
	QoL assessment	CRF	
	Sexual function scale	CRF	
	Ovarian reserve function	CRF	
Ten to 14 days after RT	Operation details	CRF	Research centers
	Residual urine	CRF	
	Perioperative complications	CRF	
Four weeks after RT	Postoperative complications	CRF	
	Pathological report	CRF	
Four months after RT	Urodynamic assessment	CRF	Research centers
	Anorectal manometry	CRF	
	QoL assessment	CRF	
	Ovarian reserve function	CRF	
	Postoperative adjuvant therapy	CRF	
	Data curation	Database	Main center
Every 12 months after RT	Urodynamic assessment	CRF	Research centers
	Anorectal manometry	CRF	
	QoL assessment	CRF	
	Sexual function scale	CRF	
	Ovarian reserve function	CRF	
	Pregnant desires and outcomes	CRF	
	Survival outcome	CRF	
	Data curation	Database	Main center
	Follow-up time, scheme, and results	Database	

*CRF* case report form, *QoL* quality of life, *RT* radical trachelectomy

This trial will be conducted in compliance with the current version of the protocol, with all statutory and regulatory requirements. The Data Safety Monitoring Committee (Supplementary Table 2) will regularly receive study data, including complications, patient conditions, and survival outcomes. This committee will be composed of physicians, administration staff, and scientific researchers, who are not participating in the study as investigators and who will be provided with available collected data during the study. The committee reserves the right to terminate the study at any time for medical or administrative reasons. In the case of loss to follow-up, the surgeons or investigators will do their best to contact each patient involved to identify if he/she is alive. If an individual leaves the research study prematurely, data related to the participant can still be used unless an objection was recorded when the patient signed the consent form. If consent is withdrawn, no data about the individual may be used unless the patient states in writing that he/she does not object.

For participants who consent to participate the trial but deviate from intervention protocols, i.e., refuse the randomized allocation, the surgical and follow-up data will still be collected the same as participants following the protocol, which will be analyzed according to intention to treat.

The trial results will be communicated to the funders, investigators, and other relevant groups via publications, reporting results in databases, data sharing arrangements, and social media (WeChat).

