## Methods

### Design

The present investigation is a randomized, controlled, noninferiority, two-arm trial comparing the efficacy of different surgical approaches of RT on the oncology and fertility outcomes in Chinese patients with early-stage CC (Figs. 1 and 2). A total of 28 domestic centers will recruit 414 patients (207 per group) from December 31, 2018, to December 31, 2020. All the surgeries are to be performed by the specialists designated in the research center (the primary investigators are listed in Supplementary Table 1). The patients are randomized on the day of written consent obtainment by the random data website (http://random.your-data.cn:8095/random), which assigns each patient a randomization number. Specified surgeons from all centers are in charge of enrolling participants. When one potential eligible patient is enrolled, her information will be sent to [name], who will generate the allocation sequence and assign participants to interventions. The allocation, together with treatment information, will be discussed with the patient by her surgeons when patients attend the clinic to get results, and relevant informed consent will be signed. On the consent form, participants will be asked if they agree to the use of their data should they choose to withdraw from the trial. Participants will also be asked for permission for the research team to share relevant data with people from the universities taking part in the research or from regulatory authorities, where relevant. This trial does not involve collecting biological specimens for storage. Model consent form and other related documentation given to participants and authorized surrogates are available from the corresponding author on request.

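### The only preoperative quality-of-life and sexual-function questionnaires are timed to surgery, not to randomisation, so the schedule lets them be completed after the woman knows her arm

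*Protocol article*

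**What the plan says.** **Timing of the questionnaires.** One sentence under Data management in the Protocol article covers the questionnaires, ovarian reserve, urodynamics and anorectal manometry together, and gives their timing by the words "will be assessed within 4 weeks before surgery, at 4 months postoperatively". The first block of Table 1 lists the QoL assessment and the sexual function scale under "Within 4 weeks before RT". This is the only preoperative assessment of either.

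**Timing of randomisation and disclosure.** Under Design: "The patients are randomized on the day of written consent obtainment by the random data website". The same section continues: "The allocation, together with treatment information, will be discussed with the patient by her surgeons when patients attend the clinic to get results". The relevant consent is signed in connection with that conversation.

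**Blinding.** Under Description of the parameters for assessing efficacy endpoints: "Obviously, a double-blinded trial was not feasible". Only those who handle the data analysis are blinded.

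**Outcomes concerned.** The secondary endpoints include "QoL assessment comprising the authorized Chinese edition of EORTC QLQ-C30", together with QLQ-CX24, the FSFI and the PFIQ-7. All are self-reported.

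**The concern.** A baseline measure is useful in a randomised comparison because the allocation cannot have influenced it. That holds if it is taken before randomisation, or at least before the participant learns the result. Here the window is tied to an event that comes after both.

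The arm label is not neutral in this trial. The Background reports worse survival with minimally invasive radical hysterectomy and the controversy that followed. The Discussion lists expected recovery benefits of the minimally invasive route and possible fertility drawbacks of the open route. The surgeon explains method and risks to the patient. A woman who has just been told her route could plausibly answer items on worry, emotional function or sexual function differently from one told the other route, before any operation.

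If that happens, a difference caused by allocation sits in the preoperative score. Subtracting or adjusting for that score then removes part of the allocation effect, or adds a spurious one. No later analysis plan can recover a pre-allocation measurement that was never taken.

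**Working it through.** The plan states no figure to reproduce. The check concerns the order of events, followed by an illustration that rests on assumptions.

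**Order of events**

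| Event | Timing stated | Section |
|---|---|---|
| Randomisation | Day of written consent | Design |
| Arm discussed with patient | Clinic visit before surgery, linked to signing consent | Design |
| Preoperative questionnaires | Within 4 weeks before surgery | Data management; Table 1 |
| Surgery | After all of these | – |

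1. Randomisation and disclosure both precede surgery. The questionnaire window is counted back from surgery and makes no reference to either.
2. Completion before randomisation and completion after disclosure can therefore both comply.
3. If surgery falls more than 4 weeks after the consent day, a questionnaire completed before randomisation lies outside the window, and only one completed after randomisation complies. The document gives no interval from consent to surgery, so how often this arises is unknown.
4. The share of women answering after disclosure is therefore undetermined, from 0% to 100%.

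**How a shift would carry through**

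Let τ be the effect of allocation on the postoperative score, d the between-arm difference that knowledge of the arm produces in the preoperative score, and β the slope of postoperative on preoperative score. In expectation:

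- postoperative scores alone: τ, with no bias;
- change scores: τ − d, a bias of size d;
- baseline-adjusted comparison: τ − βd, a bias of size βd.

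**Illustration (assumptions, not document figures)**

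The assumptions are a 0-100 scale, SD 20 to 25, β = 0.5 with equal SDs before and after surgery (so correlation 0.5), and d between 0 and 5 points. I take 166 women per arm, borrowed from the disease-free-survival calculation (165 and 166 before the 20% allowance for loss).

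- Standard error of a difference in means: SD × √(2/166) = 0.1098 × SD, which is 2.20 for SD 20 and 2.74 for SD 25. At correlation 0.5 the SD of a change score equals the SD of a single score, so the same standard errors apply to change scores.
- Adjusted standard error: multiply by √(1 − 0.5²) = 0.866, giving 1.90 and 2.38.

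| d | Change score: bias, in SE | Adjusted: bias, in SE |
|---|---|---|
| 0 | 0 | 0 |
| 2.5 | 2.5 points, 0.9–1.1 | 1.25 points, 0.5–0.7 |
| 5 | 5 points, 1.8–2.3 | 2.5 points, 1.1–1.3 |

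d is the between-arm difference averaged over all women, so it shrinks if only some answer after disclosure.

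**The case against.** **The order may be fixed elsewhere.** The article refers to a SPIRIT figure whose content is not available here, and it condenses a fuller protocol (version 3.0). A window before surgery is compatible with completion before randomisation, and nothing in the text contradicts that. This stands as a limit: the article permits late completion but does not show that it occurs. It does not remove the point, because the article gives the timing twice, in text and in Table 1, and both times ties it to surgery.

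**No affected analysis is named.** Statistics gives t tests for continuous variables and mentions neither change scores nor baseline adjustment for QoL. The word baseline is not used for this assessment. This also stands, so the harm is conditional. Even so, it is the only preoperative measurement, and use as a baseline is its natural purpose.

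**Every postoperative questionnaire is also answered with the arm known.** True, and this fix does not alter that. It protects only the preoperative value.

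**Stronger readings that the document does not support.** A reader might infer that the baseline is in fact contaminated, or that the bias is about two standard errors. Neither follows: the exposed share is unknown, and the 5-point shift, the SDs and the slope have no source in the document. A reader might also infer that women who refuse their allocation would never give a preoperative questionnaire. The document does not say so. It undertakes to collect their surgical and follow-up data in the same way as for others, and it is silent on their preoperative forms.

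**Conclusion.** The point holds as a weakness in the stated schedule. The rule allows the only preoperative QoL and sexual-function questionnaires to be completed after the woman knows her arm, in a trial where she is not blinded.

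What follows is conditional. If those scores are used as baseline for change scores or adjustment, the secondary patient-reported comparisons could be biased by an amount that the document does not allow one to derive. The illustrated figures show only that a modest shift would not be negligible against the likely standard error; a zero shift is equally compatible with what is written.

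The primary disease-free-survival comparison and comparisons of postoperative scores alone are not affected. This is a cheap improvement to secondary endpoints, not a threat to the trial's main conclusion.

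**What to change.** 1. Under Data management and in the first block of Table 1, separate the questionnaires from the functional tests. Require the QoL assessment and sexual function scale after consent to the trial and before randomisation and any disclosure of the arm. This replaces the 4-week window for the questionnaires. Urodynamics, manometry and ovarian reserve may keep it.
2. Under Design, make clear which signature is consent to the trial and that it comes before randomisation, since the present text also links a signature to the allocation discussion.
3. Hold release of the allocation in the web randomisation system until the questionnaire forms are entered in the web case report form.
4. Record the dates of questionnaire completion and of disclosure. Women already enrolled whose questionnaires followed disclosure can then be identified in a sensitivity analysis.

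**Cost.** The consent visit becomes slightly longer; no visit or procedure is added and the sample size does not change. Recruitment began in December 2018, so this is an amendment during recruitment. Under the protocol's own rules it needs evaluation by the primary investigator, approval by a plenary session of all participating centres (28) and a registry update. The cohort will then contain two timing rules, which is why the dates in item 4 matter.
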